## Discussion

To our knowledge, this is the first multicenter RCT aiming at long-term efficacy and prognosis of TCM granules with chemotherapy in ES-SCLC patients. Two published cohort research [15, 17] have reached an opposite conclusion about whether TCM decoctions can improve the PFS of ES-SCLC. Apart from the fact that both of their sample sizes were too small to be credible, they all made TCM as the only intervention but ignored the possibilities for patients choosing standard regimens simultaneously, which was not quite consistent with the present treatment status of ES-SCLC in China. Another RCT [18] of 80 SCLC cases demonstrated that TCM decoctions with standard EP could achieve a higher DCR versus EP alone. However, the study did not explain its randomization and blind. We suspect it may be an open-label trial, for no placebo was found. More crucially, the study did not stratify the limited and extensive stage in statistical analysis, which reduced the reference value of the results. Despite the lack of stringent design, the above studies have all affirmed the effectiveness of TCM on SCLC, especially in improving QoL. By contrast, our study does have several strengthens and innovations. First of all, this is a multicenter, randomized, single-blind, placebo-controlled clinical trial. The processes of grouping and single-blind are clear and well-documented. And the participants are from six grade-A tertiary hospitals in China, ensuring the representation of samples. The data are collected and managed on EDC, under the oversight of an independent monitoring organization, which is related to the credibility of our future findings. Secondly, our sample size is larger than previous similar studies. Thirdly, we focus on the role of TCM in prognosis, not just in reducing the toxicity or improving the QoL. The survival benefit is the key to judge TCM’s necessity in the treatment of ES-SCLC. And our study will solve the mystery. In addition, the multiple prescriptions in TCM regimens were designed for the common syndrome types of ES-SCLC, so as to realize the potentials and advantages of TCM syndrome differentiation.

The study still has some limitations as follows. First, the study was not designed as a double-blind trial. The traditional double-blind double-mimic method is not affordable and suitable for this study of multiple TCM prescriptions. Therefore, we finally chose single-blind which conforms to the complexity and feasibility of TCM and implemented it strictly to control the risk of reveals. Second, the assessment of OS may be influenced by confounders. Since the study intents to evaluate the long-term efficacy of TCM granules with chemotherapy, the TCM intervention period is designed as 4–6 cycles, synchronizing with chemotherapy. While in recent years, the second-line or later regimens are continuously refreshed by ICIs [19], anlotinib [20], lurbinectedin [21], and rovalpituzumab tesirine (Rova-T) [22]. As the study gives priority to the patient’s interests, the investigators should respect participants’ choices of positive treatment after PD. Thus, the second- and third-line regimen may become vital factors for prognosis. As a remedy, we require the investigators to keep detailed records of regimen participants using after PD and provide them to statisticians to build a more realistic and reasonable regression model.

In conclusion, the study’s result will provide a high-level evidence for TCM granules using with chemotherapy on the first-line treatment of ES-SCLC.

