### Statistical analysis

All data will be processed by a two-sided statistical test in SAS software 9.2 (the installation site’s authorization number: 11202165). *P*≤0.05 is defined as a statistical significance. Full analysis set (FAS), per-protocol set (PPS), and safety set (SS) will be created after data collection.

The statistical design is as follows:

For characteristics at baseline, continuous variables will be described with the use of mean (standard deviation) or median (quartile) based on the distribution. A T-test will be adopted if the normality and homogeneity of variance are satisfied; otherwise, the nonparametric test will be carried out. Categorical variables will be analyzed by the chi-square test or nonparametric test.

For OS and PFS, the Kaplan-Meier curve and the Log-rank test will be used to analyze the distribution of the survival function. And the factors selected in the univariate analysis will be brought into the Cox regression for further multivariate analysis.

For tumor response, the logistic regression or Ridit analysis will be used to compare the differences in ORR, while the proportion of CR, PR, SD, and PD will be compared by the CHM test because of the central effect.

For QoL and tumor markers, the T-test or RMANOVA will be used to compare the differences intra- or inter-groups if the two groups’ scores at baseline are similar. Or the covariance analysis will be used to correct for confounders if not.

For safety assessment, the AEs and their incidences should be recorded in detail.

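### The stated remedy for later-line therapy points to adjusting the OS Cox model for a post-randomisation variable, which can bias the adjusted hazard ratio in either direction; the log-rank comparison is unaffected

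*Protocol article*

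**What the plan says.** Three places in the protocol article bear on this.

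- **Statistical analysis.** The OS comparison comes first: "For OS and PFS, the Kaplan-Meier curve and the Log-rank test will be used to analyze the distribution of the survival function". Then "the factors selected in the univariate analysis will be brought into the Cox regression for further multivariate analysis". Nothing restricts these factors to variables measured at or before randomisation, and the section does not say which OS result governs the conclusion.
- **Discussion, limitations.** The article says that "the assessment of OS may be influenced by confounders" and that "the second- and third-line regimen may become vital factors for prognosis". It explains that "the investigators should respect participants’ choices of positive treatment after PD". The remedy is that investigators must "keep detailed records of regimen participants using after PD and provide them to statisticians to build a more realistic and reasonable regression model".
- **Sample size calculation.** The trial is powered on a two-sided log-rank test, with median OS of 8 months on chemotherapy and 4 months more with TCM.

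Two facts about conduct matter as well. Under Randomization and allocation concealment, the group is reported back to the investigator, and only participants and statistical analysts are blinded. Under Secondary outcomes, progression is assessed by the investigators.

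**The concern.** Later-line therapy is chosen after randomisation and after progression. It cannot confound a randomised comparison, because nothing that happens later can have influenced the allocation. It lies downstream of the assigned treatment, and a patient must live long enough to start it. Used as an ordinary covariate, it marks patients already known to have survived to a certain point (immortal time). Its frequency may also differ by arm, because the granules affect progression or because investigators who know the arm call progression or choose the next treatment differently.

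The screening rule makes entry into the model likely. Recipients live longer by construction, so the indicator will look prognostic even if the therapy does nothing.

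At stake is the adjusted hazard ratio for OS, the primary endpoint. The Discussion presents the model containing later-line therapy as the more realistic one, which invites readers to prefer it to the randomised comparison.

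**Working it through.** **What can be checked.** The article gives no later-line uptake, no timing of later lines and no ratio of progression time to survival time, so there is no stated figure to reproduce. The check asks whether adjustment can move the hazard ratio when the truth is no effect, and by how much.

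**Inputs from the article.** 135 per arm, 1:1; median OS 8 months; two-sided 0.05; accrual 24 months; total time 36 months in the sample size section. By the calendar dates, recruitment opens on 20 June 2019 and follow-up ends on 31 December 2021, about 30.4 months.

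**Assumptions.** OS is exponential with median 8 months in both arms (true HR 1.00). Later-line therapy has no effect. Uptake and timing are assumed as shown below.

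**Model 1: start of later-line therapy independent of survival time, received only if alive at the start.** Total time 36 months, 1,500 trials per row. For exponential times with medians m (start) and 8 (death), the chance of starting before death is (1/m)/(1/m + 1/8) = 8/(8 + m).

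- m = 5: 8/13 = 0.615. At 70%, 50% and 80% offered, receipt is 0.43, 0.31 and 0.49.
- m = 7.5: 8/15.5 = 0.516. At 80% offered, receipt is 0.41.

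The simulated receipt was 0.43, 0.30, 0.49 and 0.40; end-of-study censoring trims it slightly.

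| Control vs TCM | HR, treatment only | HR with ever/never covariate | False benefit | False harm |
|---|---|---|---|---|
| No difference (70% vs 70%) | 1.00 | 1.00 | 3.0% | 2.7% |
| Offered 70% vs 50% | 1.00 | 0.89 | 14.4% | 0.5% |
| Offered 80% vs 50% | 1.00 | 0.83 | 28.3% | 0.0% |
| Offered 80% both, start at median 5 vs 7.5 months | 1.00 | 0.92 | 10.4% | 0.7% |
| Offered 50% vs 70% | 1.00 | 1.12 | 0.6% | 14.1% |

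The nominal rate is 2.5% on each side. Without the covariate, false benefit was 1.8-2.9% and false harm 2.2-3.5%.

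The reason is simple. Recipients have low mortality because they had to survive to be treated. If the control arm has more of them, the model expects control to do better. OS is in fact equal, so the model credits TCM with the difference.

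**Model 2: progression at a Beta-distributed fraction of survival time; second line given to 90% of those living more than 2 months beyond progression.** Total time 30.4 months, 1,000 trials per row, mean fraction 0.60 in control.

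| Mean fraction on TCM | Two-sided rejection, adjusted | Adjusted HR |
|---|---|---|
| 0.60 | 7.2% | – |
| 0.65 | 7.8% | – |
| 0.70 | 14.1% | 0.90 |
| 0.75 | 19.7% | 0.86 |

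Unadjusted rejection was 4.6-6.5%. Repeats with a Beta concentration of 10 gave adjusted HRs of 1.00 at 0.60, 0.96 at 0.65, 0.92-0.93 at 0.70 and 0.86-0.87 at 0.75. Rejection was 6.2% at 0.65, 11.9% at 0.70 and 15.6% at 0.75. The inert second-line indicator was significant univariately in at least 99% of trials, so the screening rule would admit it almost every time.

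**Coding matters.** A time-varying indicator removed the bias in Model 1. It did not in a further model that tied progression time to survival time (1,000 trials, true HR 1.00). There it gave HR 0.90 with 10.6% false benefit when uptake was 50% vs 65%, and HR 1.31 with 48.9% false harm when progression came later on TCM. In that same model the ever/never covariate did little (HR 0.98-1.02). Neither the size nor the sign can be known in advance.

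**Scale.** The design hazard ratio is 8/12 = 0.667 under exponential survival. On the log scale, ln 0.83/ln 0.667 = 0.186/0.405 = 0.46 and ln 0.92/ln 0.667 = 0.083/0.405 = 0.21. In Model 1 the spurious benefit was therefore about a fifth to nearly a half of the effect the trial was designed to find.

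**The case against.** Four points can be made for the plan.

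1. **The log-rank test is listed first and the trial is powered on it.** This stands. Recording or modelling later-line therapy leaves that result unchanged, and the Cox model is described as a further analysis. A reader might infer that the primary test is compromised; the article does not support that.
2. **The form of the model is not stated.** This stands in part. The Discussion does not say Cox, ever/never or time-varying, and weighting methods for treatment switching would need the same records. An analysis plan that is not shown might name one. But calling the regimens confounders and prognostic factors is the language of covariate adjustment, and the only OS regression described is a screened Cox model with no baseline restriction. The rationale is wrong as stated, whatever the unseen detail.
3. **The bias is conditional.** This stands. It needs an arm difference in progression timing or later-line uptake, it is small when the difference is small, and it can run towards harm or hide a real benefit. A reader might infer that the plan will produce a false survival benefit; the document gives no uptake or timing from which that could be shown. A difference is nevertheless plausible, since investigators know the arm and assess progression, and PFS is an endpoint on which TCM is being tested.
4. **Part of the remedy is already there.** OS runs from randomisation to death, withdrawn participants are to be followed as far as possible, a full analysis set is planned, and nothing censors OS at later therapy. This stands and makes the fix small.

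**Conclusion.** Wrong as written; should be fixed. The article treats a post-randomisation variable as a confounder of a randomised comparison and sends it to a regression model for OS. Read with the Statistical analysis section, this points to a Cox model adjusted for later-line therapy.

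The randomised log-rank comparison is sound and unaffected; the fault lies in the adjusted hazard ratio and in any conclusion drawn from it. If later-line therapy enters as an ever/never covariate and the arms differ clearly in its uptake or in progression timing, a true hazard ratio of 1.00 came out at about 0.83-0.93, or about 1.12 when the imbalance was reversed. False-positive rates were about 10-28%. With no arm difference there was little or no bias.

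These sizes rest wholly on assumed uptake and timing, an inert later-line therapy and exponential survival. They show what can happen, not what will. That the model will take this form is a reading of two sections together, not an explicit statement.

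**What to change.** State the following before unblinding:

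- The OS conclusion rests on the log-rank comparison of all randomised patients as assigned, counting every death whatever therapy followed progression.
- The Cox model for OS uses pre-specified baseline covariates only, in place of univariate screening over an open list.
- Later-line therapy is tabulated by arm: type, number of lines and time from randomisation to start.
- If an estimate that addresses later-line therapy is wanted, one method is named in advance with its assumptions (for example inverse-probability-of-censoring weighting). It is labelled supportive and does not drive the conclusion. A time-varying indicator alone is not enough.

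The Discussion sentence should stop calling later-line regimens confounders and describe them as events after randomisation.

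The cost is about one paragraph in the analysis plan. The post-progression records already required serve the tabulation, and sample size and visits are unchanged. A weighting analysis would also need time-updated covariates that predict switching, so the sponsor should check that they are recorded before naming it.

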## Trial status

The trial is conducted according to the protocol (Version 2.0, 4 June 2019). It is currently enrolling participants. The recruitment began on 20 June 2019 and was expected to be completed on 19 June 2021. The first participant was enrolled on 4 September 2019.

## Data Availability

Not applicable.
